| Tumor tissue sample**^17^** | **X** | |  |  | **X** |  |  |
| **Notes:**   1. The screening period has a window of 28 days, the treatment period has a window of ±3 days (with a tumor assessment window of ±7 days), the end-of-treatment visit has a window of ±7 days, and the follow-up period has a window of ±7 days. During the screening period, ECOG performance status, hematology, blood biochemistry, coagulation, urinalysis, T3 or FT3, FT4, and TSH must be recorded within 7 days prior to the first dose and meet the corresponding inclusion and exclusion criteria for enrollment. 2. All prior treatments within 30 days before signing the ICF and all concomitant treatments from the signing of the ICF until the discontinuation of study treatment will be documented; thereafter, concomitant treatments for SAEs related to the study drug need to be documented. 3. Height examination is only performed in the screening period; vital signs include body temperature, pulse, respiratory rate and blood pressure. Body weight will be measured prior to each dose. If the subject's weight during the study changes by ≤10% compared to the baseline reference weight, no dose adjustment of the study drug is required. If the weight change exceeds 10%, the dose needs to be recalculated. 4. AEs and SAEs should be recorded from the signing of the ICF until 30 days after the last dose of the study drug. 5. Gastroscopy and pathology tests: Subjects must complete gastroscopy and pathology tests during the screening period after meeting the enrollment criteria and signing the informed consent form to determine the distance between the tumor and the incisors and collect tumor tissue specimens for subsequent laboratory tests. If gastroscopy and pathology tests have been performed at an external institution, gastroscopy must be repeated at this study site, but there are no requirements for pathology tests. 6. PD-L1 expression of gastric cancer: Subjects must complete the immunohistochemical PD-L1 expression and CPS scoring of gastric cancer tissues during the screening period after meeting the inclusion criteria and signing the informed consent form. They need to be completed at this study site. 7. MSI status of gastric cancer: Subjects must complete the immunohistochemical MSI status testing of gastric cancer tissues during the screening period after meeting the inclusion criteria and signing the informed consent form. They need to be completed at this study site. 8. Serplulimab will be administered on Day 1 of each 3-week treatment cycle after completion of all clinical and laboratory procedures/assessments. During the neoadjuvant phase, treatment consists of 3 cycles with a dose volume of 300 mg/dose. The dosing window is within ±3 days of the scheduled time point. 9. After completion of all clinical and laboratory procedures/evaluations, neoadjuvant therapy will be administered using the standard SOX regimen (oxaliplatin + Tegafur), with 3 weeks as one treatment cycle, and neoadjuvant therapy consists of a total of 3 cycles. Oxaliplatin will be administered on Day 1 of each cycle at a dose of 130 mg/m^2^, via intravenous infusion over 2–6 hours (chemotherapy drugs will be administered after the completion of Serplulimab infusion). If the body surface area exceeds 2.0 m^2^, the dose is calculated based on 2.0 m^2^. Tegafur will be administered orally according to the body surface area as below: <1.25 m^2^, 40 mg/dose; ≥1.25 to <1.5 m^2^, 50 mg/dose; ≥1.5 m^2^, 60 mg/dose; twice daily, from Day 1 to Day 14 of each treatment cycle. 10. After completion of all clinical and laboratory procedures/assessments, thymalfasin 4.8 mg will be administered via subcutaneous injection, twice weekly starting from Day 1 of neoadjuvant therapy. On Day 1 and Day 4 of each week during Weeks 1–9. 11. Routine laboratory tests include hematology, blood biochemistry, urinalysis, and coagulation function. The hematology items include complete blood count with differential. The blood biochemistry items include blood urea/urea nitrogen, creatinine, sodium, potassium, magnesium, chloride, bicarbonate/carbon dioxide combining power/total carbon dioxide (TCO2), calcium, phosphorus, glucose, total bilirubin, direct bilirubin, alanine aminotransferase (ALT), aspartate aminotransferase (AST), alkaline phosphatase, lactate dehydrogenase, total cholesterol, total protein, and albumin. The urinalysis items include specific gravity, pH, glucose, protein, casts, ketones, and blood cells. Coagulation function tests include activated partial thromboplastin time (APTT), prothrombin time (PT), and international normalized ratio (INR). The tests should be performed within 7 days before the first dose, within 3 days before dosing in Cycle 3, within 7 days before surgery, and within 3–7 days after surgery. If the laboratory tests and study drug administration are scheduled on the same day, the study drug cannot be administered until the test results are obtained. The analysis will be conducted in this study site. 12. Thyroid function tests include analysis of triiodothyronine (T3 or FT3), thyroxine (T4 or FT4), and thyroid-stimulating hormone (TSH). The tests should be performed 7 days before the first dose, 3 days before dosing in Cycle 3, 7 days before surgery, and within 3–7 days after surgery. The analysis will be conducted in this study site. 13. Cardiac function markers include: myocardial enzymes [creatine kinase (CK) and its isoenzymes], troponin (TnT or TnI), and brain natriuretic peptide (BNP and/or NT-proBNP). The tests should be performed 7 days before the first dose, 3 days before dosing in Cycle 3, 7 days before surgery, and within 3–7 days after surgery. The analysis will be conducted in this study site. 14. Tumor markers must include: carcinoembryonic antigen (CEA), carbohydrate antigen CA19-9, and alpha-fetoprotein (AFP). The tests should be performed 7 days before the first dose, 3 days before dosing in Cycle 3, 7 days before surgery, and within 3–7 days after surgery. The analysis will be conducted in this study site. 15. Pre-transfusion eight-item panel: All subjects must undergo hepatitis B surface antigen (HBsAg) and hepatitis B core antibody (HBcAb) testing during the screening period. For subjects with HBsAg (+) or HBcAb (+), further hepatitis B virus (HBV) DNA titer testing is required. At screening (baseline), in case of HBV DNA (-), and either 1. HBsAg (+), or 2. HBcAb (+), HBsAg (-), then HBV surface antigen/core antibody and HBV DNA must be tested every 2 cycles during treatment, before the surgery, at treatment discontinuation, and during safety follow-up. 16. CT or MRI imaging examinations should be performed within the screening period, within 7 days before treatment in Cycle 3 of neoadjuvant therapy, within 1 week after completion of neoadjuvant therapy, and after the surgery until the initiation of adjuvant therapy (recommended 4–12 weeks after the surgery). Throughout the study period, the examination methods should remain as consistent as possible. Abdominal CT scans require dual-phase (arterial and venous) imaging, performed under fasting conditions with the intake of at least 1000 mL of water or contrast agent. Contrast agents should be used unless contraindicated. The investigator assesses tumor imaging findings according to RECIST v1.1 (the frequency of tumor assessments may be increased as clinically needed at the investigator's discretion). The investigator should determine subsequent treatment based on the efficacy evaluation results. If tumor assessment has been performed within 28 days prior to the first dose, and the same method and equipment are used at the same hospital, it may serve as the baseline tumor assessment. 17. Subjects must provide formalin-fixed, paraffin-embedded (FFPE) tumor samples (paraffin blocks or unstained sections) collected from the lesion site at or after GC diagnosis (preferably within 2 months before the first dose of the study drug), along with relevant pathological reports of the aforementioned specimens. If the subject does not have archived tumor tissue samples that meet the requirements, a fresh tumor lesion biopsy must be performed during the screening period to obtain corresponding tumor samples (the number of specimens collected will be determined based on the biopsy). Additionally, surgically excised tumor tissue specimens will be retained postoperatively. Tumor tissue section samples will be used for determination of PD-L1 expression levels and MSI testing. | | | | | | | |

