Imaging examinations will be performed to evaluate efficacy and feasibility of surgery after the completion of Cycles 2 and 3 of neoadjuvant therapy (within 7 days before the start of Cycle 3 and within 7 days after the end of Cycle 3). Imaging examinations are conducted after surgery and prior to adjuvant therapy, and pathological assessment will also be performed to evaluate the completeness of surgery. Evaluation requires a full abdominal direct contrast-enhanced (iodinated contrast) CT scan and gastric tumor MRI (contrast-enhanced). The same imaging technique should be used for pre- and post-evaluation in the same patient, and all imaging data must be retained. Patients who experience PD may continue the study treatment if they are willing and deemed suitable by the investigator to continue the original treatment regimen after re-signing the informed consent form, and re-evaluation will be performed after 4 weeks; otherwise, the patients will discontinue the study. For patients who discontinue treatment due to intolerable toxicity, if no efficacy evaluation is performed within 4 weeks prior to discontinuation, an efficacy evaluation should be conducted at the time of discontinuation.

For patients with potentially resectable gastric cancer after neoadjuvant therapy, surgery is scheduled within Weeks 2–6 after the completion of the last chemotherapy + immunotherapy. The surgical approach is determined based on the degree of disease response, including R0 resection, R1 resection, or cytoreductive surgery. The postoperative efficacy evaluation criteria primarily focus on surgical pathological assessment (complete pathological response rate, major pathological response rate, tumor regression grade, R0 resection rate, etc.), supplemented by imaging evaluation (objective response rate, disease control rate) for reference. At this point, the study has achieved its primary endpoint.

1. **Safety Reports and Adverse Event Management**
   1. **Definition of Adverse Event**

An adverse event (AE) is defined as any unfavorable and unintended medical occurrence in a clinical study participant from the time of signing the informed consent form, whether or not considered related to the study drug. AEs include, but are not limited to, the following circumstances:

- Exacerbation of pre-existing (prior to entering the clinical trial) medical conditions/diseases (including exacerbation of symptoms, signs, and abnormal laboratory findings);

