- Any new adverse medical condition (including symptoms, signs, newly diagnosed diseases);
- Clinically significant abnormal laboratory findings.
  1. **Definition of Serious Adverse Events**

A serious adverse event (SAE) refers to any AE that meets at least one of the following criteria:

- Resulting in death, excluding deaths due to disease progression of the studied indication.
- Life-threatening (the term "life-threatening" in the definition refers to an AE that places the subject at immediate risk of death when it occurs, and does not include AEs that may lead to death only if they worsen).
- Requiring inpatient hospitalization or prolongation of existing hospitalization, excluding:
- Hospitalization in rehabilitation facility
- Hospitalization in sanatorium
- Routine admission by emergency department
- Day surgery (e.g., outpatient/day/ambulatory surgery)
- Hospitalization or prolonged hospitalization not related to the worsening of an AE is not considered an SAE. For example: Hospitalization due to pre-existing conditions without the occurrence of new AEs or exacerbation of the original disease (e.g., abnormal laboratory results persisting before the clinical trial); hospitalization for other reasons (e.g., annual routine physical examinations); hospitalizations specified by the clinical study protocol during the study (e.g., procedures required by the protocol); elective hospitalizations not related to the worsening of AEs (e.g., elective surgeries); scheduled treatments or surgical procedures (should be documented in the overall trial protocol and/or the subject's baseline data); hospitalization solely for the administration of blood products.
- Resulting in persistent or significant disability/incapacity.
- Lead to congenital anomaly/birth defect.
- Other important medical events: defined as events that jeopardize the subject or require medical intervention to prevent any of the aforementioned situations.
  1. **Definition of Adverse Event**

The investigator will evaluate all AEs according to the National Cancer Institute Common Terminology Criteria for Adverse Events (CTCAE) Version 5.0. Any AEs with CTCAE grade changes will be recorded in the Adverse Event Case Report Form/Worksheet.

All AEs, regardless of CTCAE grade, must be evaluated for whether they constitute SAEs.

Evaluation criteria for AEs are as follows:

Table. Evaluation Criteria for Adverse Events

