All AEs, including SAEs, observed by the investigator or spontaneously reported by subjects from the signing of the informed consent form until 30 days post-surgery, will be collected.

- - 1. **Follow-up of adverse events**

AEs should be followed up until they return to baseline or Grade 0–1, or until the investigator deems further follow-up unnecessary for justified reasons (e.g., the AE cannot resolve or has improved). If the AE cannot resolve, a reasonable explanation must be documented in the CRF. Regardless of whether it is related to the study drug, the recovery status and date of the subject's AE or SAE should be recorded in the CRF and medical records.

- - 1. **Recording content of AEs**

The investigator must fully document any AE, including diagnosis (or symptoms, signs, and abnormal laboratory findings if no diagnosis is available), start and end dates and times (if applicable), CTCAE severity grade and changes (for Grade 3 or higher events), whether it is a SAE, measures taken regarding the study drug, treatments administered for the AE, outcome of the event, and the relationship between the AE and the study drug.

For any SAE, the investigator should also provide the date when the AE meets SAE criteria, the date when the investigator becomes aware of the SAE, the basis for classifying the AE as an SAE, dates of hospitalization and discharge, possible cause of death, date of death, whether an autopsy is performed, causality assessment with the study procedures, causality assessment with other medications, and other potential causes leading to the SAE.

The investigator should also provide the rationale for causality assessment and a description of the SAE. In the SAE description, the following must be included: subject No., age, sex, height, and weight; the indication for the study drug treatment, disease stage, and relevant systemic conditions; the clinical course of the SAE, including its onset, progression, outcome, and final result; laboratory test results related to the SAE (the test time, units, and normal reference ranges must be provided); medical history related to the SAE, comorbidities, and their onset and duration; medication history related to the SAE, concomitant medications, and details of their initiation, duration, and dosage and administration; as well as detailed information on the study drug treatment, including its initiation, duration, dosage and administration.

The description of AE records is as follows:

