**Death**

All deaths occurring during the entire study, including the 30-day follow-up period after the last dose, regardless of their relationship to the study drug, should be recorded in the Death Report Form of the CRF and promptly reported to the sponsor.

When recording death events, if the cause of death is clearly identified, the cause of death shall be documented as an AE, with the outcome of the AE being death, and the event shall be reported as a SAE (deaths due to tumor progression or deaths occurring 30 days after the last dose that are considered not related to the study drug, and are not recorded or reported as AEs/SAEs; however, the investigator shall document the death in the Death Report Form of the CRF and promptly notify the sponsor). If the cause of death is unknown at the time of reporting, it shall be recorded as "death of unknown cause" in the Adverse Event Form of the CRF, and "death of unknown cause" shall initially be reported as an SAE, followed by further investigation to determine the exact cause of death.

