**Reporting of SAEs:**

The reporting period for SAEs is from the signing of the informed consent to 30 days after surgery (inclusive). In the event of an SAE, whether it is an initial report or a follow-up report, the investigator must promptly complete the Serious Adverse Event Report Form, sign and date it, and report it to the sponsor within 24 hours of becoming aware of the event. Meanwhile, SAEs occurring after using Henlius products shall be reported to Henlius: ([contact]) within 24 hours after awareness, and the SAE occurring after using SciClone products shall be reported to SciClone ([contact]) within 24 hours after awareness.

If a SAE occurring outside the aforementioned period is determined to be related to the study drug, it should also be reported.

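### The Death paragraph of Section 11.4 exempts from AE/SAE recording some unrelated postoperative deaths that Sections 11.2, 11.4 and 11.5 make recordable and reportable to 30 days after surgery

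*Protocol*

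**What the plan says.** The Death paragraph of Section 11.4 sets aside two kinds of death: those from tumour progression, and those "30 days after the last dose that are considered not related to the study drug, and are not recorded or reported as AEs/SAEs". The same sentence continues: "however, the investigator shall document the death in the Death Report Form of the CRF and promptly notify the sponsor". The paragraph opens with a general rule that all deaths, "regardless of their relationship to the study drug, should be recorded in the Death Report Form of the CRF and promptly reported to the sponsor".

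Other parts of the protocol set different rules for the same event:

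- Section 11.1 defines an AE "whether or not considered related to the study drug". It gives no end date.
- Section 11.2 makes an event an SAE if it is fatal: "Resulting in death, excluding deaths due to disease progression of the studied indication". It has no exception for deaths unrelated to study drug.
- Section 11.4, on collection and time frame, says that all AEs including SAEs, "from the signing of the informed consent form until 30 days post-surgery, will be collected".
- Section 11.5 gives the SAE reporting period the same end point, 30 days after surgery inclusive. Only outside that period does reporting depend on a relationship to study drug.
- Note 4 of the Study Flow Chart gives a third statement: "AEs and SAEs should be recorded from the signing of the ICF until 30 days after the last dose of the study drug".

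**The concern.** An unrelated death late in the postoperative month falls under two rules that cannot both be followed. Under Sections 11.2 and 11.5 it is an SAE to be reported within 24 hours. Under the Death paragraph it is neither an AE nor an SAE. A fatal complication of gastrectomy is the obvious example, because an investigator is likely to attribute it to the operation and not to the study drug.

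The rule matters because other steps are triggered by SAE status. Section 11.5 requires SAEs to be sent to both drug manufacturers, whereas the Death paragraph names only the sponsor. Section 13 requires SAEs to be reported promptly to the ethics committee. Section 2.2 sets out to observe any adverse event in all patients, so the all-cause listing would lack its most serious entry. There is also an odd asymmetry: a serious non-fatal complication on a given postoperative day is reportable, yet a fatal one judged unrelated may not be.

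The exemption combines a time limit with a causality judgement. Note 4 is a time limit only, so correcting Note 4 alone would leave the exemption in force.

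**Working it through.** The protocol states no figure to reproduce. The check is date arithmetic on its schedule.

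**Inputs**

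- Three 21-day cycles (Section 6.2): third infusion on study day 1 + 2 × 21 = 43.
- Tegafur on Days 1–14 of each cycle: last Tegafur day 43 + 13 = 56.
- Thymalfasin on Days 1 and 4 of Weeks 1–9: Week 9 Day 4 is 8 × 7 + 4 = day 60. The Synopsis row on administration adds the option of continuing until surgery; flow-chart Note 10 and Sections 3 and 6.2 do not.
- Surgery 2–6 weeks after the third dose (Synopsis, Study Design; Section 3): s = 14 to 42 days after day 43.
- The protocol does not define *last dose*. I read the exemption as covering deaths more than 30 days after it, which is the natural sense but an interpretation.

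**Formula**

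Let L be the study day of the last dose. The Section 11.5 window ends on day 43 + s + 30. The exemption begins after day L + 30. The number of the 30 postoperative days on which the rules conflict is

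d(s) = min(30, max(0, 43 + s − L)).

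**Results**

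| Last dose taken as | L | s = 14 | s = 28 | s = 42 | Mean over s = 14 to 42 |
|---|---|---|---|---|---|
| Third infusion | 43 | 14 | 28 | 30 | 734/29 = 25.3 (84%) |
| Last Tegafur day | 56 | 1 | 15 | 29 | 435/29 = 15.0 (50%) |
| Thymalfasin Week 9 Day 4 | 60 | 0 | 11 | 25 | 325/29 = 11.2 (37%) |

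The sums behind the means are:

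- Third infusion: (14 + … + 30) + 12 × 30 = 374 + 360 = 734.
- Last Tegafur day: 1 + … + 29 = 435.
- Thymalfasin Week 9 Day 4: 1 + … + 25 = 325.

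The means give each of the 29 possible surgery days equal weight, which is an assumption. If thymalfasin continues until surgery, its doses are 3 or 4 days apart, so d is a few days at most.

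The Synopsis row on administration and Sections 6.2 and 10 time surgery from the completion of chemotherapy plus immunotherapy. If that means the last Tegafur day, surgery falls on days 56 + 14 = 70 to 56 + 42 = 98. The interval between the two cut-offs then becomes 27–55, 14–42 and 10–38 days for the three rows, of which at most 30 are postoperative days within the window.

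**Scale of one event.** With 30 planned subjects, one unrecorded death is 1/30 = 3.3 percentage points. The protocol gives no expected number of such deaths, so no expected loss can be computed.

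**After alignment.** If the exemption began only after 30 days from surgery, d(s) = 0 in every row.

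**The case against.** The strongest reply is that these deaths are not lost. They stay on the Death Report Form with prompt notice to the sponsor. Section 6.3 follows complications for 30 days after surgery, the Synopsis grades surgery-related safety separately, and OS counts death from any cause. A death of unknown cause is still first reported as an SAE. All of this stands. A reader might infer that surgical deaths drop out of the safety results altogether, and the documents do not support that.

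Second, the complication that leads to death is itself an AE within the Section 11.4 window, and it is an SAE if it is life-threatening or prolongs hospitalization. It would often have been reported before the death. This also stands: the exemption bites fully only when death comes before any such report. It does not remove the contradiction over the fatal event.

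Third, the drug-safety rates are largely untouched. The Synopsis names treatment-related AEs, those of Grade 3 or higher, and immune-related AEs. Deaths judged unrelated do not belong in these. The incidence named in Section 2.2 is for Grades 3–4, which omits fatal events. So a claim that these rates are biased downward fails; what is affected is the all-cause AE/SAE record.

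Fourth, the 84% figure is tempting as a headline but holds only if the last dose is the third infusion. Thymalfasin is a named study drug given later, and under that reading the share is 37% or close to zero.

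**Conclusion.** The contradiction is real and the Death paragraph is wrong as written. For an unrelated, non-progression death more than 30 days after the last dose but within 30 days of surgery, Sections 11.2, 11.4 (collection) and 11.5 require an SAE record and report, and the Death paragraph forbids both. The loss is confined to the all-cause AE/SAE record and the reports that SAE status triggers.

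The exposure runs from almost none to all 30 postoperative days, depending on the date of surgery and on which drug's dose counts as last. No single percentage should be quoted without stating both. Any expected number of affected deaths would be a guess.

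This is an inconsistency in safety recording, worth correcting because the event is grave and the correction small. It does not bear on the primary endpoint.

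**What to change.** Reconcile the Death paragraph, and flow-chart Note 4 with it, to the window already set in Sections 11.4 and 11.5:

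- Limit the exemption to deaths due to tumour progression and to unrelated deaths after the window has ended, that is, more than 30 days after surgery.
- Record every other death as a fatal AE/SAE, whatever the judged relationship to study drug.
- For subjects who never undergo surgery, state the end of the window explicitly; otherwise a window tied to surgery has no end for them. One option is to keep the existing 30 days after the last dose, specified as the last dose of any study drug.

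The Death Report Form and the notice to the sponsor stay as they are. The cost is one reworded sentence in Section 11.4, the matching edit to Note 4, an instruction to the site, and at most a few extra SAE reports. No treatment rule changes.
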